**The main specific purposes and hypotheses are:**

1. To test what is the effectiveness of tailored counseling to minimize inactivity periods and increase physical activity in persons involved in sitting-related work. *H: Counseling increases physical activity and decreases muscle inactivity time during workday and leisure time*
2. To test if the counseling can induce long term behavioral changes that benefit health?

*H: Counseling induces behavioral changes that last long time. Positive effects in health related markers such as serum lipids and blood pressure can be seen at 6 and 12 months after counseling.*

1. To examine what is the effectiveness of parental counseling on children’s physical activity behavior? *H: There is transfer effect of parental counseling so that also the children’s physical activity has increased.*

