**Methods**

**Design.** A cluster randomized controlled intervention will be performed on parents that sit more than 50% of the work time. The intervention group will receive tailored counseling to decrease time in sitting position and increase daily activity, especially the non-exercise activity. Children aged 3-8 will be included to the study and their physical activity will be objectively monitored before and three times after the parental counseling.

**Subjects.** Eligible participants are parents with work that primarily includes sitting. *Inclusion criteria*: healthy men and women with children 3-8 years old, and having work where they sit more than 50% of their work time. *Exclusion criteria*: self-reported chronic, long-term musculoskeletal disease or progressive neurological disease, diagnosed cardiovascular or metabolic disease with regular medication, families with pregnant mother at baseline, BMI>35, children confined to a wheelchair or bed. The recruitment will be performed in Jyväskylä region delivering advertisements to parents via kindergartens and primary schools. To avoid contamination of treatment the randomization will be done regionally before recruitment and the control group will not be informed about the intervention. Both the intervention and control groups will include areas from the city center and suburbs of Jyväskylä.

**Sample size.** From the preliminary results it can be expected that small changes in behavior can effectively decrease the longest inactivity periods and total inactivity time as example in Fig.2 shows. Based on decrease in the inactivity periods by behavioral changes the sample size of 10 would be sufficient to show statistically significant changes. However, we also aim that the intervention has significant health effects. Thus, it was estimated that increase of 0.2 mmol/l in high-density lipoprotein after 6 or 12 months of intervention can be possible with the intervention. The required sample size to show this effect would be 77. Adding the cluster effect (Cambell et al. 2004) and drop-outs we estimate that 100 subjects in both groups would be needed.

Fig 2. Histogram of daily muscle activity time (% of whole day activity) divided in sections 0-5% of maximum (MVC). Women n=6, 30 measurement days, men n=6, 26 measurement days. The women performed more non-exercise activity than men and it is significantly reflected to the main outcome. **p<0,01, ***p<0,001 (Haakana 2010).

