**Ethics.** We will submit the study plan with questionnaires and informed consent for evaluation by the local ethics committee. The RCT will not begin before approval has been received. Subjects will be volunteers with right to withdraw from the study at any time without consequences. The study will be conducted according to good scientific practice.

**Protocol.** The protocol of the study is shown in Fig. 3. Before counseling the parents will be measured for baseline data (fasting blood samples, anthropometry, questionnaires, physical fitness test) and a representative normal day EMG activity with other measures of physical activity level. After counseling the representative day with agreed behavioral changes will be measured again using EMG and other devices for physical activity level assessment. In the first 3 months the compliance will be reinforced by phone calls and possible modifications to the agreed intervention will be made. Between 3 to 6 months the compliance will be followed once a month and no contact with the subjects will be made in the maintenance period. The midline and endline measurements include fasting measurements, questionnaires and 24-hour heart rate recordings. Control group participates only in baseline and normal day measurements, midline and endline measurements. Children will be measured at baseline, after 3, 6, 9 and 12 months for physical activity behavior using triaxial accelerometers (Actigraf).

Figure 3. Timeline of the project showing the timing of physical activity (PA) measurements for parents and children.

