After counseling the research personnel will phone the subjects two times to ask about the compliance of the goals set and send e-mails. This reinforcement period lasts 6 months. The end measurements at 12 months are made to assess the maintenance of the habitual changes and effects on health markers. During the last 6 months there will not be researcher contact other than 9 months measurements with the subjects.

The control group will not receive the counseling intervention but will undergo the measurements similarly as the intervention group. The counseling does not include dietary counseling. The subjects will be monitored for dietary changes by questionnaires but eating habits are assumed to be maintained the same.

**Statistical analysis**. The EMG activity variables such as total inactivity time during day and mean intensity of EMG will be used to categorize people into quartiles according to 1) physical activity and 2) health marker indexes. Chi Square will be used to compare EMG distributions and levels to other variables. The difference in physiological signals between categories will be compared using One-way/Multivariate ANOVA. Correlation and regression analysis will be used to retrieve relationships between physical and health conditions and physical activity assessments. Repeated measures ANOVA will be used to determine effects of intervention complemented with mixed model ANOVA in case of missing data points.

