**Timetable**

Data collection for RCT baseline will begin in spring 2011 and continued through 2012 during spring and fall seasons. The seasonal variations in the subjects beginning the study in fall or spring will be different; however, during the baseline and endline measurements the weather allows similar outdoor activities.

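### The intervention effect is given both a repeated measures ANOVA and a conditional mixed model, with neither named as primary although drop-outs are expected

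*Protocol*

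**What the plan says.** The Statistical analysis paragraph gives one sentence to the trial comparison. It names repeated measures ANOVA for the intervention effect, "complemented with mixed model ANOVA in case of missing data points". It does not state which result is primary when both are produced, how the baseline value enters, or which visit contrasts are reported.

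Three other places bear on it:

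- The sample size paragraph under Methods raises 77 to 100 for the cluster effect and attrition: "drop-outs we estimate that 100 subjects in both groups would be needed".
- The second hypothesis is tied to particular times: "Positive effects in health related markers such as serum lipids and blood pressure can be seen at 6 and 12 months after counseling".
- The Timetable says "The seasonal variations in the subjects beginning the study in fall or spring will be different", then adds that outdoor conditions are comparable at the baseline and 12-month visits.

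Regions are allocated before anyone is recruited (Methods, Subjects).

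**The concern.** Two analyses are named for one effect, and the second depends on a condition that the protocol itself expects to be met. The word chosen for the mixed model suggests that it is run in addition to the ANOVA, not in its place. Two estimates and two p-values would then exist for each outcome, with no rule for which one is the trial's answer.

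The method named first is also the weaker fit. In its usual form, repeated measures ANOVA needs complete records, counts baseline among the responses and returns one pooled group-by-time test. The protocol separates the two follow-up times in substance: contact with participants continues to 6 months and largely stops afterwards. The 6-month and 12-month differences therefore answer different questions, and a pooled test reports neither. If attrition differs between the counseled and control arms, the two analyses can also disagree in the estimate as well as the p-value.

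**Working it through.** **Inputs.** From the protocol: 77 and 100 (sample size); adult health markers at baseline, 6 and 12 months; children's accelerometry at baseline, 3, 6, 9 and 12 months; EMG at baseline and about one week after counseling. Not given, so assumed: two-sided alpha 0.05, power 80% or 90%, correlation r of 0.5 to 0.9, drop-out of 10% or 20%, and 5% to 10% missed per visit.

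**1. The plan's own figure.** The 77 can be neither reproduced nor refuted, because SD, alpha and power are not stated. Solving n = 2(z_alpha/2 + z_beta)²SD²/0.2² for SD gives 0.443 (80% power) or 0.383 (90%) if 77 is per group, and 0.313 or 0.271 if it is the total. The allowance can be examined. Taking 77 and 100 both as per group, 100/77 = 1.30. That covers at most 1 − 77/100 = 23% drop-out with no cluster effect or, for example, 10% drop-out with a design effect of 100 × 0.90/77 = 1.17. The split is not stated, but missing data are planned for.

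**2. How far the two analysis sets differ.** If misses are independent between visits, adults with both follow-ups are 0.95² = 90% to 0.90² = 81%, and children with all four are 0.95⁴ = 81% to 0.90⁴ = 66%. If the same people miss every visit, completers are 95% to 90% in both groups. The truth probably lies between.

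**3. What the ANOVA tests.** Group-by-time degrees of freedom with two arms are the number of visits minus 1: adults' health markers 3 − 1 = 2, children 5 − 1 = 4, EMG 2 − 1 = 1. Only the EMG comparison is already a single contrast.

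**4. Choosing between the analyses.** Null simulation: 4,000 runs per setting, 100 per arm, three visits, equal correlation between visits treated as known, random drop-out and no clustering. Rejection rates at a nominal 5%:

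| r | Drop-out | Completers only | All data | Smaller p |
|---|---|---|---|---|
| 0.6 | 10% | 5.4% | 5.2% | 6.3% |
| 0.6 | 20% | 4.9% | 5.4% | 6.3% |
| 0.8 | 10% | 5.0% | 4.9% | 5.8% |
| 0.8 | 20% | 4.6% | 4.6% | 5.6% |

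The Monte Carlo standard error is about 0.4 points.

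**5. Precision.** With baseline as a response level and one follow-up, the group-by-time test equals a change-score test. In units of SD², its variance is 2(1 − r); with baseline as covariate it is 1 − r². The ratio is (1 − r²)/[2(1 − r)] = (1 + r)/2.

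| r | Change | Adjusted | Ratio | Extra standard error of change |
|---|---|---|---|---|
| 0.5 | 1.00 | 0.75 | 0.75 | 15.5% |
| 0.7 | 0.60 | 0.51 | 0.85 | 8.5% |
| 0.8 | 0.40 | 0.36 | 0.90 | 5.4% |
| 0.9 | 0.20 | 0.19 | 0.95 | 2.6% |

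For the mean of two follow-ups the ratio is 0.67 at r = 0.5, 0.80 at 0.7 and 0.87 at 0.8. With 77 per arm and SD 0.443 (the per-group, 80% power reading in step 1), power for change versus adjusted is 80% versus 90% at r = 0.5, and 95% versus 98% at r = 0.7.

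**The case against.** A reader might infer that the plan discards incomplete participants. It does not: the quoted clause brings in the mixed model for exactly that case, and such a model keeps people with partial data. What remains is that the all-data model is a conditional add-on when it should be the stated main analysis.

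The protocol does not say that baseline is a response; that is inferred from the method's name. Nor is it an error in itself, since a mixed model with baseline in the response vector and a common baseline mean matches the efficiency of covariate adjustment. Baseline handling and contrasts may also be left to an SAP. This stands, so the precision point is conditional. Naming two analyses without ranking them is still something the protocol itself does.

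A reader might take the variance ratio as 5% to 33% more subjects for free (1/0.95 = 1.05; 1/0.75 = 1.33). The formula assumes independent subjects and comparable arms. Here regions are allocated before recruitment, so arms may differ at baseline, and adjusted and change-score analyses can then give different answers. That caveat stands.

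The trigger for the mixed model is missingness, not the result, and the inflation from choosing is small. Both are true.

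A reader might also conclude that season is left uncontrolled. The Timetable addresses baseline and endline. Only the 3-, 6- and 9-month visits are exposed, and the arm comparison is biased there only if entry season differs by arm, which the document does not show.

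**Conclusion.** The point holds in a limited form. The protocol specifies two analyses of the intervention effect, expects the condition that brings in the second, and fixes neither as primary. The one named first, in its usual form, rests on completers and does not deliver the 6- and 12-month differences that the hypotheses call for.

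The size is moderate. Type I error is about 5.6% to 6.3% if the smaller p-value is always taken, under random drop-out and no clustering. If baseline is handled as a response level, adjustment would have 0.75 to 0.95 of the variance of a change-from-baseline test with one follow-up, for an assumed r of 0.5 to 0.9, comparable arms and no clustering. The documents do not support saying that participants are thrown away, that the error rate is badly inflated, or that season has been ignored. Confidence is high that the primary analysis is unfixed, and lower on the amount of precision at stake.

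**What to change.** Make one linear mixed model the sole main analysis, whether or not data are missing:

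- **Data:** all available follow-up values, analysed as allocated.
- **Terms:** baseline value as covariate; arm by visit, with visit categorical; region, the unit randomised, as a random effect (regions sit within arms, so fixed region effects would absorb the arm effect); and family where participants share one.
- **Contrasts:** between-arm differences at 6 and 12 months for health markers; at 3, 6, 9 and 12 months for children's activity; and at the post-counseling day for EMG, as a baseline-adjusted comparison with one follow-up. The EMG contrast needs a second recording day in controls. The Protocol paragraph ("Control group participates only in baseline and normal day measurements, midline and endline measurements") and the later statement that controls are measured in the same way as the intervention group should be reconciled on this.
- **Season:** entry season may be added as a covariate, mainly for the 3-, 6- and 9-month visits.
- **Sensitivity:** keep repeated measures ANOVA on completers only in this role.

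The model itself needs no new data beyond the measurements planned. The cost is protocol or SAP wording, a few extra model terms and reliance on a missing-at-random assumption, which should be stated.

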**Measurements**

[figure not shown]
**Short term main outcome is the physical activity (PA) behavior**. In parents it will be assessed with EMG, triaxial accelerometer and questionnaires. ***EMG*** will be measured using shorts with embedded textile electrodes (Suunto Oy, Vantaa, Finland / Megaelectronics Ltd., Kuopio, Finland) measuring activity from 4 thigh muscles during normal daily life and laboratory tests (Fig. 4). The measurement system has been tested for validity, repeatability and feasibility in our laboratory (Finni et al. 2007). The data is collected to a 52 g module in the waist in raw form with sampling frequency of 1000Hz. The raw EMG signal is rectified and averaged over 100 ms non-overlapping intervals. The signals are stored in a module for off line-analysis. The EMG data will be analyzed for inactivity period times and frequencies as well as for total inactivity. This analysis will be repeated using different signal levels (1%, 2%, 5% of maximum voluntary contraction) for detection of the inactivity periods. Activity histograms and on-off analysis will be performed. Burst analysis (Kern et al. 2001) will be used to quantify activity periods.

In a sub group of children we test the use of EMG shorts as measurement tool of physical activity.

Fig. 4. Shorts that are used to collect muscle EMG activity from thigh muscles.

***Acceleration.*** Triaxial acceleration will be collected during all the measurements (Alive heart monitor, Alive technologies, Australia) and be used to compare the activity counts with EMG levels for validation purposes. **In children** the PA behavior will be measured using triaxial accelerometer (Actigraf) that the children wear on their waist for one week at pre, 3, 6, 9 and 12 months after counseling intervention to parents. During this one week period, the parents will fill in diary of the childrens physical activities. In addition, children’s basic motor skills will be tested three times during the intervention.

***Questionnaires.*** From the detailed 7-day physical activity questionnaire focusing on non-exercise activity the daily MET values will be calculated for the past year at baseline and endline (modified from Lakka et al. 1997). During the days of data collection, the subjects fill in detailed physical activity diaries that reveal standing up from sitting position, walked up stairs etc.

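### The protocol leaves open whether repeated measures ANOVA or the mixed model decides the intervention effect when visits are missing, so a completers-only result could carry the conclusion

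*Protocol*

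**What the plan says.** The Statistical analysis paragraph gives one sentence to the effect of the intervention: "Repeated measures ANOVA will be used to determine effects of intervention complemented with mixed model ANOVA in case of missing data points". The mixed model enters only through the closing words, "complemented with mixed model ANOVA in case of missing data points". The paragraph does not say which result is reported as the trial's finding if both are run.

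Drop-out is expected. The Sample size paragraph ends: "Adding the cluster effect (Cambell et al. 2004) and drop-outs we estimate that 100 subjects in both groups would be needed". No rate is given.

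The number of measurements differs by outcome:

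- **Parents' health markers:** baseline, 6 months and 12 months. Under the Protocol subheading: "The midline and endline measurements include fasting measurements, questionnaires and 24-hour heart rate recordings".
- **Children's accelerometry:** five waves, which the children "wear on their waist for one week at pre, 3, 6, 9 and 12 months after counseling intervention to parents".
- **EMG:** two recording days. Counselling comes about a week after baseline and the second recording a week after counselling.

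**The concern.** A standard repeated measures ANOVA needs a complete row for each participant. A parent who attends at 6 months but not at 12 loses the 6-month value as well. A likelihood-based mixed model keeps it. With missing visits the two methods therefore describe different groups, one of them selected after allocation.

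Two things are at stake. First, if the order of the analyses is not fixed, the choice between two results can be made after both are seen. Second, drop-out could be lopsided. Only counselled parents sign an agreement to change their behaviour and are telephoned about keeping to it. Leaving because the agreed changes did not work out can happen in that arm alone, and completers would then flatter counselling.

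**Working it through.** **1. The plan's own figures.** The target is an "increase of 0.2 mmol/l in high-density lipoprotein after 6 or 12 months of intervention", and "The required sample size to show this effect would be 77". SD, alpha and power are not given, so 77 cannot be reproduced. It can only be solved backwards. Taking 77 per arm, two-sided 5% and 80% power:

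SD = 0.2 / [(1.960 + 0.842) × √(2/77)] = 0.443 mmol/l, so the target is 0.2/0.443 = 0.45 SD.

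If 77 is the total (38.5 per arm), SD = 0.313 and the target is 0.64 SD.

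Reading 100 as per group, the inflation is 100/77 = 1.299. With no clustering at all, this covers at most 1 − 77/100 = 23% drop-out. With 20% drop-out it leaves 100 × 0.80/77 = 1.039 for the design effect. So 20%, used below, is near the most that the plan can absorb on this reading.

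**2. How many have complete series.** Assume baseline is always present and a share m misses each follow-up visit independently. The complete share is (1 − m)^k, with k = 2 follow-ups for parents' markers and k = 4 for the children.

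| m (assumed) | Parents, k = 2 | Children, k = 4 |
|---|---|---|
| 5% | 90% | 81% |
| 10% | 81% | 66% |
| 15% | 72% | 52% |
| 20% | 64% | 41% |

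**3. Completer bias with no true effect.** This is a simulation of large arms with three visits, equal correlation r = 0.7 and 20% drop-out per arm between 6 and 12 months. The log-odds of drop-out fall by the stated slope per outcome SD of 0-to-6-month change. Entries are the false benefit among completers.

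| Slope, counselled | Slope, control | 6 months | 12 months |
|---|---|---|---|
| 1.5 | 0 | 0.15 SD | 0.07 SD |
| 1.5 | 0.75 | 0.06 SD | 0.03 SD |
| 0.5 | 0 | 0.06 SD | 0.03 SD |
| 1.5 | 1.5 | 0 | 0 |
| 0 | 0 | 0 | 0 |

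The likelihood estimate using all visits stays at zero in every row, because drop-out here depends only on values already observed. Keeping the steepest contrast (1.5 against 0) and varying r from 0.5 to 0.8 and drop-out from 10% to 25% moves the 6-month figure between about 0.06 and 0.28 SD.

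**4. With the planned effect present.** Take a true effect of 0.2 mmol/l, SD 0.443, r = 0.7, 100 per arm, and drop-out tied to poor change in the counselled arm only (log-odds 1 per SD of change). At 12 months:

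| Overall drop-out | Completers | Likelihood |
|---|---|---|
| 12% | 0.223 | 0.203 |
| 22% | 0.233 | 0.199 |
| 31% | 0.248 | 0.201 |

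With the same slope in both arms, both estimates stay at about 0.20. The spread of the two estimates is nearly equal (0.053 for both at 22% drop-out). At 12 months the gain from the mixed model is therefore protection against bias, not precision.

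**The case against.** The plan brings in the mixed model in exactly the situation complained of. In a short plan written for an ethics committee, the sentence can fairly be read as ANOVA when data are complete and the mixed model otherwise. A reader might infer that the headline effect is a completer result. The document does not support that: it names no headline estimate and nowhere limits the analysis to completers.

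A reader might also infer that the ANOVA result will be biased. That is not supported either. The bias needs drop-out that is related to outcome and differs between arms, and the protocol gives no drop-out data. The design makes the mechanism plausible and no more.

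The order of analyses is often left to a statistical analysis plan, which is not at hand and may settle it. Against that, the protocol is not silent here. It assigns the intervention test to the ANOVA and calls the mixed model a complement, not a replacement. A later plan would have to override that sentence, not just add detail to it.

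Two further limits stand. Counting baseline as a visit that can be missed gives 0.9³ = 73% of parents and 0.9⁵ = 59% of children complete, but this overstates the loss because baseline is the entry measurement. And the attrition argument has little force for EMG, with two recordings about two weeks apart.

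**Conclusion.** The point holds in a limited form. The protocol expects drop-outs, names first a method that in its standard form discards incomplete participants, and does not say which of its two models carries the conclusion. The 6- and 12-month markers and the children's series could therefore be concluded from completers, and the choice stays open until the data are seen.

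Under step 3's assumptions at r = 0.7 and 20% drop-out, unequal outcome-related drop-out gives a false benefit of about 0.06 to 0.15 SD at 6 months and 0.03 to 0.07 SD at 12 months. Against a target of 0.45 SD (77 per arm, 80% power) that is 13% to 33% at 6 months and 7% to 16% at 12 months. It is nil when drop-out is unrelated to outcome or equally related in both arms. If drop-out depends on values never observed, the mixed model is not guaranteed to be unbiased either. This is a worthwhile correction at no cost, not evidence that the planned result would be wrong.

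**What to change.** Replace the sentence on the intervention effect with:

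*The intervention effect on outcomes measured at follow-up visits will be estimated by a likelihood-based linear mixed model using every available visit of every participant, analysed in the arm of their area and with a random effect for area, whether or not data are missing; a completers-only analysis is shown only as a sensitivity analysis.*

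The area term belongs in the sentence because randomization is by region, and a single model without it would ignore the clustering that the sample size claims to allow for. The two-day EMG comparison can be specified separately.

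The cost is one sentence. The mixed model is already in the plan, and no extra data are needed.
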